## Abstract

**Background:**

Surgery remains the gold standard for management of endometriosis, offering significant improvement in patient pelvic pain and quality of life (QoL). Postoperative tissue adhesions can however diminish these benefits, limiting the long-term effectiveness of the intervention. Despite the development of strategies and devices to reduce adhesion formation, their efficacy remains inconclusive.

**Objective:**

This study aims to propose and evaluate a novel approach involving early visceral mobilization and training of patients in abdominal self-mobilization as a means to improve QoL following surgery.

**Methods:**

This pilot study is a prospective, randomized, phase II superiority trial. Patients undergoing surgery for infiltrating endometriosis will be randomized, with a 2:1 ratio, into two groups. The intervention group (n = 42) will receive six sessions of osteopathic visceral mobilization with training in abdominal self-mobilization techniques, one preoperative, and five postoperative during the first month post-surgery. The control group (n = 21) will receive no osteopathic visceral mobilizations but will be offered an osteopathic session after one year. The primary endpoint is a minimum increase of 20 points (on a 100-point scale) in the Endometriosis Health Profile-30 (EHP-30) global score, at one year. Secondary endpoints include assessment of gastrointestinal quality of life (GIQLI), sexual function (FSFI), urinary symptoms (ICIQ-FLUTS), pain catastrophizing (PCS), as well as scar examination, pelvic pain, abdominal flexibility, use of medical and non-medical care, analgesic and hormonal treatments, pregnancy rate, physical activity, sedentary lifestyle and patient compliance. Statistical analyses will be based on a one-sided α=0.05 and β=0.15, assuming a standard deviation of 25 points in the EHP-30 global score. A total of 42 participants in the intervention group and 21 in the control group are required.

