### Sample size

The required number of subjects is based on a comparison between the two randomized groups (experimental group *vs*. control) of the percentage variation in EHP-30 questionnaire scores between the pre-operative visit and at 1 year, with a two-sided first-species risk of error of 5%. For ethical reasons, we chose a 2:1 ratio for randomization.

In the literature, Goncalves et al. reported on the evolution of EHP30 scores (before/after) for a control and treatment group receiving an intervention (yoga sessions) [43]. Variations were small in the control group for the 5 main EHP-30 dimensions, and ranged from 20 to 35 points for the treatment group. Pokrzywinski et al [44]. showed the same before/after differences for a control and treatment group (Elagolix molecule), and defined thresholds of between 20 and 35 points for clinically significant differences.

To demonstrate a difference of 20 points associated with a standard deviation of 25, in percentage variation for EHP-30 questionnaire scores between the pre-operative visit and 1 year, with a statistical power greater than 80%, 38 patients are required in the experimental group and 19 in the control group. To allow for patients leaving the protocol and loss to follow-up, 10% more patients are required in each group. Thus, a total of 63 patients will be recruited (42 in the experimental group and 21 in the control group).

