### Statistical methods

Statistical analyses will be carried out using R software (R Core Team (2022). R: A language and environment for statistical computing. R Foundation for Statistical Computing, Vienna, Austria. URL https://www.R-project.org/.).

Descriptions are given in number (N) and percentage (%) for qualitative variables, and in mean and standard deviation (SD) or median and interquartile range for quantitative variables, according to their distributions (Gaussian or not). Missing data will be quantified. Normality will be analyzed using the Shapiro-Wilk test and histograms.

Patients will be described and compared between groups at inclusion according to compliance with eligibility criteria, epidemiological characteristics and clinical features. A description of protocol deviations, patients allocated according to these deviations and reasons for drop-out will also be provided.

Initial comparability of the two groups will be assessed on the main patient characteristics and potential factors associated with the primary endpoint. Any difference between the two groups relating to these characteristics will be determined on the basis of clinical and statistical considerations.

Comparisons between groups will be made systematically 1) without adjustment 2) by adjusting for those factors for which distribution may be unbalanced between groups despite randomization, such as contraception, level of disease severity and post-operative complications. All statistical tests will be performed using a two-sided alpha level of 5%. Certain analyses involving secondary endpoints will be mainly exploratory in nature. As discussed by Feise et al. [47] adjustment of alpha risk will not be proposed systematically, but on a case-by-case basis in the light of clinical and statistical considerations.

The main analysis will be carried out on an intention-to-treat basis. An intention-to-treat population refers to all randomized patients except those for whom consent is not obtained or who withdraw their consent concerning use of their data. A per-protocol analysis will be considered of all randomized patients except for those with one or more major deviations defined as: patients ineligibility, uncompliant patients in the experimental group (less than once a day on average over the first post-operative month), or control group patients who perform visceral mobilizations more than 4 times during the year of their own initiative.

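### The abstract sets a one-sided 5% test and the body a two-sided 5% test, so the primary comparison has two incompatible success thresholds; the body's rule is the one that reproduces the sample size

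*Protocol article*

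**What the plan says.** Three places in the protocol article fix the error level.

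- **Abstract, Methods:** "Statistical analyses will be based on a one-sided α=0.05 and β=0.15", continuing "assuming a standard deviation of 25 points in the EHP-30 global score". The endpoint is described as "a minimum increase of 20 points (on a 100-point scale"). The size follows directly: "A total of 42 participants in the intervention group and 21 in the control group are required".
- **Sample size:** the comparison of the two groups is planned "with a two-sided first-species risk of error of 5" per cent. Then: "To demonstrate a difference of 20 points associated with a standard deviation of 25", "with a statistical power greater than 80%, 38 patients are required in the experimental group and 19 in the control group". Ten per cent is added in each group for losses, giving 42 and 21, 63 in all.
- **Statistical methods:** "All statistical tests will be performed using a two-sided alpha level of 5" per cent. The same part of the article names a Student's t test or a Wilcoxon test for the main comparison, reported with 95% confidence intervals.

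**The concern.** The abstract's sentence speaks of the analyses, not only of the sizing, and the Statistical methods sentence covers every test. Both therefore claim the primary comparison, and they set different thresholds. A one-sided 5% test has the same critical value in the favourable direction as a two-sided 10% test.

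The Discussion makes a later large-scale study conditional on the expected results being observed. With two published thresholds, the choice between them could be made after the data are known. The abstract is also the most widely read part of the article, and it carries the more lenient rule.

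A second question follows: do the abstract's own inputs lead to the 42/21 it calls required? If not, that helps to show which statement actually sized the trial.

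**Working it through.** **Inputs.** Difference 20, SD 25 (standardised difference 20/25 = 0.80) and 2:1 allocation. The abstract adds one-sided 0.05 and power 85%; the Sample size section adds two-sided 5%, power above 80% and 10% extra per group.

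**Formula (normal approximation).** Control n = 1.5 × [25 × (z_α + z_power) / 20]²; the experimental group is twice that. The factor 1.5 is 1 + 1/2 for 2:1 allocation.

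**Step 1: the body's figure.** Two-sided 5%, 80% power:

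- 1.5 × [25 × (1.960 + 0.842)/20]² = 18.4, so 19 control and 38 experimental.
- Adding 10%: 38 × 1.1 = 41.8 → 42; 19 × 1.1 = 20.9 → 21. Total 63.

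This reproduces the stated figures. By the noncentral t, 38/19 has 79.9% power, a shade under the stated level, and the plain t requirement would be 40/20. The body therefore reproduces by the normal approximation specifically.

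**Step 2: the abstract's inputs.** One-sided 0.05, 85% power:

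- Normal: 1.5 × [25 × (1.645 + 1.036)/20]² = 16.85, so 17 control and 34 experimental (51). With 10% added: 18.7 → 19 and 37.4 → 38 (57).
- Noncentral t: 34/17 gives 84.4% and 36/18 gives 86.2%, so 36/18 (54). With 10% added: 19.8 → 20 and 39.6 → 40 (60).

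Neither plain formula gives 42/21. The total of 63 exceeds these results by 9 to 12 patients before losses, and by 3 to 6 after adding the body's 10%.

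**Step 3: power at the two sizes, for a difference of 20 and SD 25.**

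| Evaluable | Test at 5% | Normal | Noncentral t |
|---|---|---|---|
| 38/19 | two-sided | 81.3% | 79.9% |
| 38/19 | one-sided | 88.5% | 87.8% |
| 42/21 | two-sided | 84.9% | 83.8% |
| 42/21 | one-sided | 91.1% | 90.6% |

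The entry that comes closest to 85% is 42/21 with a two-sided test and no losses. None of the one-sided entries is near 85%.

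**Step 4: the gap between the two rules.** At 38/19 the standard error of the difference is 25 × √(1/38 + 1/19) = 7.02. The smallest observed difference that counts as success is about 1.960 × 7.02 = 13.8 under the body's rule and 1.645 × 7.02 = 11.5 under the abstract's. A favourable result between these values has a two-sided p between 0.05 and 0.10, and the two rules disagree on it.

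**The case against.** The best reply is that Sample size and Statistical methods are the operative sections and agree with each other, and that the promised 95% confidence intervals fit a two-sided 5% test. An analyst following them would never use the one-sided rule. That stands as a guide to which text was probably intended. It does not reconcile the abstract, which says outright that the analyses rest on a one-sided level.

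Four stronger readings are tempting, and the document does not support them.

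- **That the two power statements contradict each other.** They do not: 85% is greater than 80%, and beta 0.15 roughly matches 42/21 two-sided with nobody lost. What can be said is that 85% is not the power expected after the losses the Sample size section itself plans for.
- **That the abstract's inputs cannot give 42/21 by any route.** They can if a Wilcoxon efficiency is assumed. The unrounded t requirement is 17.32 controls; 17.32/0.955 = 18.1, so 38/19, and 10% more gives 42/21. With the lower-bound efficiency, 17.32/0.864 = 20.05, so 42/21 before any losses. The article mentions neither adjustment, so these routes are assumptions, but they rule out a categorical claim.
- **That the abstract wrongly omits the 10% allowance.** Giving only the number to be recruited is ordinary condensation; the Sample size section states the allowance.
- **That the trial is the wrong size.** The body's number follows from its own inputs by a standard approximation.

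**Conclusion.** The sidedness conflict is wrong as written: one sentence of the abstract gives the primary test a 5% false-positive rate in the favourable direction, while the body gives it 2.5%. This rests on the wording alone and on no assumption.

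The arithmetic is supporting evidence. By the plain normal or t formula, the abstract's inputs give 34/17 or 36/18 evaluable (38/19 or 40/20 with 10% added), whereas the body's inputs give exactly 38/19 and then 42/21 by normal approximation. This points to the body as the derivation that sized the trial and to the word one-sided as the likely slip, but that is an inference; the article does not say so. With the planned losses, two-sided power is about 80% (81.3% normal, 79.9% t), and a figure of about 85% requires all 63 patients to be evaluable. These powers assume a common SD of 25 and a true difference of 20.

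**What to change.** Replace the abstract sentence with the body's rule: two-sided alpha of 5%; about 80% power on 38 + 19 evaluable patients to detect a difference of 20 with SD 25; 42 + 21 patients randomised to allow for 10% loss. Remove the one-sided level and the beta of 0.15.

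In the new sentence, express the difference and SD on the scale used in Outcomes and Sample size, which is percentage variation from the pre-operative score. Carrying over the abstract's points on the global score would leave the two parts of the article on different scales.

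The cost is one corrected sentence and a quoted power of about 80% instead of 85%. There are no extra patients and no change to design or conduct. By the article's timeline, data collection ends in January 2028, so the correction can be made before analysis.

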### Outcomes

The primary outcome is the percentage variation in baseline EHP30 questionnaire scores between the pre-operative visit and at 1 year after surgery.

To measure QoL, the authors chose the EHP-30 questionnaire, one of the most frequently used scales for quantification of perceived health, specific to endometriosis [11].

The EHP-30 contains 30 items ranging from 0 (best health status) to 100 (worst health status). The core questionnaire items are grouped into 5 main scales: pain (11 items), control and powerlessness (6 items), emotional well-being (6 items), social support (4 items) and self-image (3 items). A modular questionnaire, that may not apply to all women with endometriosis, comprises 23 items grouped into six scales: ‘Work’ (5 items), ‘Relationship with children’ (2 items), ‘Sexual intercourse’ (5 items), ‘Medical profession’ (4 items), ‘Treatment’ (3 items), and ‘Infertility’ (4 items) [7].

Secondary outcomes are listed below:

1/- a/The following validated questionnaire scores: EHP-30, GIQLI (digestive function), FSFI (sexual function), ICIQ-FLUTS (urinary tract symptoms) and PCS (pain catastrophizing) evaluated at the pre-operative visit, and at 6 and 12 months.- b/VAS of pelvic pain reported at the pre-operative visit, then post-operatively at H6, D1, 1 month, 6 and 12 months and expressed as a percentage variation compared with pre-operative visit results.-c/Post-operative examination of scar appearance by the surgeon at 6 and 12 months using the SCAR (Scar Cosmesis Assessment and Rating) scale.2/- a/VAS of abdominal flexibility in the following areas: hypogastrium, and right and left iliac fossa, at one year assessed by an independent osteopath, scores ranging from 0 to 10 (0 corresponding to normal flexibility and 10 to total rigidity).- b/Consultations in addition to conventional care (medical and non-medical)- c)Use of analgesics and hormonal treatments reported by patients during the first postoperative year-d)Pregnancy achievement during the first postoperative year3/The International Physical Activity Questionnaire (IPAQ) assessed before surgery, at 6 and 12 months after surgery.4/Short-term compliance in terms of number of days and frequency of mobilizations, assessed on a weekly basis for up to 6 weeks,. Long-term compliance is assessed monthly post-cycle in terms of whether and how often mobilizations were performed, and if used in cases of pain.

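### The SD of 25 behind the sample size is attached to the EHP-30 global score in points in the abstract and to its percentage variation in the Sample size section, so the stated power holds only under one reading

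*Protocol article*

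**What the plan says.** Three places in the protocol article bear on this point.

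- **Abstract, Methods.** The endpoint is in points: "The primary endpoint is a minimum increase of 20 points (on a 100-point scale") in the EHP-30 global score at one year. The calculation is described as "assuming a standard deviation of 25 points in the EHP-30 global score".
- **Outcomes.** "The primary outcome is the percentage variation in baseline EHP30 questionnaire scores between the pre-operative visit and at 1 year after surgery".
- **Sample size.** The planning inputs are introduced as "To demonstrate a difference of 20 points associated with a standard deviation of 25, in percentage variation for EHP-30 questionnaire scores" from before surgery to 1 year. The result is stated "with a statistical power greater than 80%, 38 patients are required in the experimental group and 19 in the control group". Adding 10% gives 42 and 21, or 63 in all.

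The Sample size section supports the difference with two cited studies. One, of a yoga intervention, is cited for before/after changes of 20 to 35 points in its treated group. The other, of a drug treatment, is cited for thresholds of 20 to 35 points for a clinically significant difference. Neither is cited for an SD. The article gives no baseline mean and no correlation between the pre-operative and 1-year scores.

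**The concern.** A score, its change in points and its percentage change are three different variables, and in general they have three different SDs. The article gives the figure 25 to the first in the abstract and to the third in the Sample size section, while the difference of 20 comes from the second.

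The SD is the only variance input to the 38 and 19. If it belongs to a variable other than the one tested, the stated power does not describe the planned analysis. In one direction, a null result from this phase II pilot would be read as stronger evidence against the intervention than it is. In the other, the trial is larger than its stated aim needs. A reader who has only the article cannot tell which.

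**Working it through.** **Inputs.** From Sample size: difference 20, SD 25, two-sided 5%, 2:1 allocation, 38 and 19 evaluable. From Statistical methods: Student's t test (or Wilcoxon), two-sided 5%. The abstract's one-sided 5% with β = 0.15 is a separate disagreement and is not used here.

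**1. Reproducing the plan's figure.** Normal approximation, control arm:

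n = (1 + 1/2) × (1.960 + 0.842)² × 25² / 20² = 1.5 × 7.85 × 1.5625 ≈ 18.4, rounded up to 19; the experimental arm is 2 × 19 = 38.

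Standard error at 38 and 19 = 25 × √(1/38 + 1/19) = 7.02, and 20 / 7.02 = 2.85. Power by normal approximation is 81.3%. By the noncentral t with 55 degrees of freedom it is 79.9%. Adding 10%: 38 × 1.10 = 41.8, rounded to 42, and 19 × 1.10 = 20.9, rounded to 21. The section is consistent with itself, with no margin: the t test needs 40 and 20 for 80%. If all 63 patients are evaluable, power is 84.9% (83.8% by the t test).

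**2. If 25 is the SD of the score, analysed as absolute change.** Assume equal SDs before surgery and at 1 year, and a pre/post correlation r. Then

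SD of change = 25 × √(2(1 − r)).

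The documents give no r, so the values below are assumptions. Power is for the two-sided 5% t test, difference 20 points, 38 and 19 evaluable. The last column is the evaluable total that gives 80% power at 2:1, against 57 planned.

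| r | SD of change | Power | Total for 80% |
|---|---|---|---|
| 0.2 | 31.6 | 60% | 93 |
| 0.3 | 29.6 | 66% | 81 |
| 0.4 | 27.4 | 72% | 69 |
| 0.5 | 25.0 | 80% | 60 |
| 0.6 | 22.4 | 88% | 48 |
| 0.7 | 19.4 | 95% | 36 |

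Example at r = 0.3: 25 × √1.4 = 29.6; standard error 29.6 × √(1/38 + 1/19) = 8.31; 20 / 8.31 = 2.41; power 66%.

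**3. If 25 is the SD of the score, analysed as percentage change.** The formula in step 2 does not apply, because each patient's change is divided by her own baseline. An illustrative simulation assumed a baseline mean of 40 to 60, score SD 25, a mean fall of 20 points, baseline scores below 10 or above 100 excluded, and 1-year scores held within 0 to 100. The SD of the percentage change was about 49 to 56 at r = 0.5, and 37 to 67 over r = 0.3 to 0.7. I give no power for this case, because the difference would change too: 20 points is 20/60 = 33% to 20/40 = 50% of such a baseline mean, not 20%. The simulation shows only that 25 and 20 cannot be carried over from points to percentages unchanged.

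**The case against.** The strongest defence is that the Sample size section is the operative text. It attaches 25 to the variable that Outcomes calls primary, and its figures reproduce. The abstract never says that its SD is for a single time point. Having defined the endpoint as an increase in the global score, it may simply be shorthand for the SD of that increase. The basis of the 25 may also be in the full protocol, which is not shown. And the power table runs on both sides of the stated figure, so it demonstrates neither a shortfall nor an excess.

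Most of this stands. It rules out calling the 38 and 19 a miscalculation, and a missing source for the SD would not be a finding by itself. It does not remove the conflict. Even if the abstract means the SD of the change, it means a change in points, while the Sample size section says percentage variation and draws its difference from studies reporting points. The article states the same input twice, for different quantities.

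A reader might also infer that the two statements agree once r is taken as 0.5. That is true only for absolute change with equal SDs at both times. It does not reconcile the abstract with a percentage variation.

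**Conclusion.** The planning SD is described inconsistently, and the stated power is conditional on one description being right. If 25 is the SD of the analysed variable, and 20 is the difference on that same variable, power at 38 and 19 is 81.3% by normal approximation and 79.9% by the t test, in line with the stated figure apart from rounding at the 80% boundary. If 25 is the SD of the score, power for absolute change is about 66% at r = 0.3, 80% at 0.5 and 95% at 0.7, given equal SDs and assumed r. For percentage change the SD could be well above 25, by an amount that depends on a baseline distribution the article does not give.

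It would be tempting to conclude that the trial is underpowered. The documents do not support that: nothing in them fixes r, and at r above 0.5 power for absolute change exceeds the stated figure. What needs correcting is the definition of the input, before the power statement is relied on.

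**What to change.** Make the abstract, Outcomes and Sample size name one primary variable in one unit. Absolute change in EHP-30 global score from the pre-operative visit to 1 year, in points, would match the source of the 20-point difference. Outcomes has to be changed with the other two; changing only the abstract and Sample size to points would create a new conflict with the primary outcome. If percentage variation is kept, the difference and the SD both need to be justified in percent.

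Then state that 25 is the SD of that variable and on what basis, and restate the power for the planned t test. With absolute change as the variable, that is about 80% at 38 and 19 if 25 is the SD of change. If 25 is the SD of the score, give a range over stated correlations, for example 66% at 0.3, 80% at 0.5 and 95% at 0.7.

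Keep 63 patients. The cost is a wording correction in three places and one recalculation. The downside is that the power statement becomes slightly less favourable, or becomes a range. Follow-up is scheduled to end in January 2028, so the correction can be made before the 1-year comparison is run.

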**Discussion:**

This trial aims to demonstrate that early and repeated osteopathic sessions following surgery for endometriosis may significantly improve patient QoL.

